## **Specialized cardiovascular and cerebrovascular evaluation**

Echocardiography: Patients will be bedded on a couch and allowed to relax for at least 15 minutes. Cardiac morphological and functional parameters will be assessed by comprehensive two-dimensional doppler echocardiography. Echocardiography data will be stored and analyzed by an investigator blinded to the patients' clinical data. Doppler imaging of the tricuspid annulus will be assessed according to standard methods. This will allow us to assess the following parameters: systolic pulmonary artery pressure (RVsys, calculated from the tricuspid regurgitation velocity by using the modified Bernoulli equation:  $RV_{sys} = 4 \times (v_{max})^2$  where  $v_{max}$  is the maximum of the regurgitation velocity jet measured over the tricuspid valve); the right and left atrial and ventricular fractional area change (%) and the tricuspid annular plain systolic excursion (mm).

**Cardiovascular and cerebrovascular control:** Measurements will be performed during a 30 min quiet rest period and during two 6 min intervals of exercise, separated by a 6 min period of rest. Submaximal constant load exercise at 50% of predicted maximal heart rate will be performed using a couch cycle-ergometer with 45% semi-recumbent position (Ergoline Ergometrics 900, Schiller AG, Switzerland) with the head stabilized by a deflatable pillow. In the studies using nocturnal oxygen supplementation (2nd part of project), the load will be kept identical during the active and sham treatment period. Resting heart rate and its variability in the high and low frequency band reflecting sympatho-vagal activation the *baroreceptor reflex* will be assessed by continuous measurement of the ECG and continuous beat by beat blood pressure by the Finapres® technique. *Quadriceps muscle tissue oxygen* will be monitored by near infrared spectroscopy (NIRO 200 NX, Hamamatsu, Shizuoka, Japan) along with peripheral pulse oximetry. In healthy volunteers, skeletal muscle deoxygenation occurs more rapidly at altitude, and it is expected that this decrease may be even more pronounced in COPD patients, thereby contributing to early onset of fatigue at altitude. Thus, the hypothesis will be tested that, for a given cardiac output, COPD patients will desaturate to a higher degree at 2590 m vs. 490 m. **Cerebrovascular blood flow:** Patients will be fitted with a mouthpiece and nose clip. Inspired gases will be sampled continuously. End-tidal (i.e., arterial) PO2 and PCO2 will be measured by gas analyzers using the technique of dynamic end-tidal forcing. The right middle cerebral artery (MCA) blood flow velocity as an index of cerebral blood flow will be measured using transcranial Doppler ultrasound (TC22, SciMed, Bristol, England). Measurements will include the maximum (VP) and intensity-weighted mean Doppler frequency shifts and the power of the Doppler signal, an index of the cross-sectional area of the vessel. Without a change in power (i.e. at a constant vessel cross-sectional area), VP is considered a reliable index of global cerebral flow. Changes in cerebral vascular tone will be calculated as cerebrovascular conductance, which is the change in VP for a given change in mean arterial pressure. Recent studies have suggested that cerebral autoregulation is impaired in COPD patients during exercise. Since cerebral autoregulation is disturbed in healthy subjects exposed to hypoxia at altitude we hypothesize that COPD patients exercising at 2590 m will reveal cerebrovascular dysfunction compared to 490 m that might be modified by oxygen administration.

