### Unblinding criteria

Investigators will be unblinded only after analyses of all data. Exceptions are serious adverse events or other conditions that require immediate knowledge on oxygen or sham treatment to allow prevention of adverse health effects to the patient.

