### **4.3 INTERVENTIONS TO MINIMISE BIAS**

The study is designed according to a randomized cross-over trial balanced for the ascent protocol during study phase 1 and to the order of the oxygen and placebo during study phase 2.

Randomization will be performed by letting patients draw an envelope from a set containing a code defining the order of interventions. Envelops will be prepared in a way that assures a balanced design in regard to oxygen/sham and pulsed/continuous oxygen/sham. All patients and investigators are blinded for oxygen/sham or vice versa during study phase 2 by the use of identically looking concentrators producing room air and oxygen.

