
## Sleep studies

Nocturnal polysomnography will be performed according to standard techniques as described previously. In addition to central EEG derivations, EOG and submental EMG, measurements include calibrated respiratory inductive plethysmography (RespiratracePT, Nims, Miami Beach, USA), pulse oximetry, end-tidal (CapnoCheck Plus, ResMed, Basel Switzerland) and transcutaneous PCO2 (Tosca, Radiometer, Basel, Switzerland), pulse transit time, nasal pressure swings, oral thermistor, NIRS of cerebral tissue oxygenation from 2 miniaturized frontal sensors, bilateral sub costal surface EMG of the diaphragm to assist in differentiation of obstructive from central apnea/hypopnea. Sleep and arousals will be scored according to standard criteria as described by Rechtschaffen und Kales and by the American Academy of Sleep Medicine guidelines. An apnea or hypopnea will be scored if the amplitude of the nasal pressure swings or the sum signal of the respiratory inductive plethysmography falls below 50% of baseline during the previous 2 minutes for >10 seconds. Obstructive will be differentiated from central events based on rib cage-abdominal asynchronous and paradoxical motion, deformations of the nasal pressure curve suggesting inspiratory flow limitation, and diaphragmatic surface EMG. The apnea/hypopnea and oxygen desaturation index (SpO2 dips >3%) will be computed as mean number of events/h.

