### **8.3 STATISTICAL ANALYSIS**

Before analysis, data are anonymized by allocating a numerical code to each participant. Completeness, plausibility and distribution of data will be assessed by inspection of numerical results and graphical display. Normality of distribution will be tested by the Shapiro Wilks statistic. Data will be summarized by means (SD) and medians (quartiles) for normal and non-normal distributions. Effects of treatment and altitude will be evaluated according to the principles of cross-over trial analysis described by Senn S. using ANOVA and multiple regression.

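### Phase 1 tests altitude, but no rule hides altitude from the readers of echocardiograms and sleep recordings, which leaves avoidable room for detection bias in some secondary outcomes

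*Protocol*

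**What the plan says.** **Echocardiography** (Protocol 6.1, specialized cardiovascular evaluation): the recordings are to be "stored and analyzed by an investigator blinded to the patients' clinical data". Altitude, location, date and visit are not mentioned. Systolic pulmonary pressure is computed as four times the squared peak velocity of the tricuspid regurgitation jet.

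**Sleep studies** (Protocol 6.1): "Sleep and arousals will be scored according to standard criteria as described by Rechtschaffen und Kales", supplemented by American Academy of Sleep Medicine guidelines. An apnea or hypopnea is a fall in nasal pressure swings or plethysmography sum signal below half of the preceding two-minute baseline for more than 10 seconds. For event type, "Obstructive will be differentiated from central events based on rib cage-abdominal asynchronous and paradoxical motion", together with the shape of the nasal pressure curve and diaphragm EMG. No masking of the scorer is stated.

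**Trial-level blinding** (Protocol 4.3): "All patients and investigators are blinded for oxygen/sham or vice versa during study phase 2". For phase 1 the section offers a "randomized cross-over trial balanced for the ascent protocol during study phase 1" and no masking.

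**Outcomes** (Protocol 4.1 and 8.1): echocardiographic pressure and dimensions, and the prevalence and type of apnea/hypopnea, are secondary outcomes in both phases.

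**The concern.** Phase 1 is a within-patient comparison of altitudes. Diagnosis, history and recruitment findings are the same at every altitude, so hiding them from the echo reader does little to protect the contrast. Hiding day-specific findings removes some clues, but what separates one patient's recordings is where and when they were made, and no rule covers that.

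Patients and site staff must know the altitude; whoever later reads a stored recording need not. If the reader does know it, expectation can shift the tracing of a Doppler envelope, the marking of a borderline hypopnea or the choice between central and obstructive. Randomized order balances period effects. It does not protect against reader expectation, which follows the altitude wherever it falls in the sequence.

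**Working it through.** The plan gives no figure on this point, so there is none to reproduce. The check is whether any provision hides altitude from a reader.

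1. *Echo rule (6.1).* It masks clinical data. It would mask altitude only if that term was meant to include the circumstances of the visit, which the text does not say.
2. *Sleep rule (6.1).* It gives scoring criteria but no masking.
3. *Section 4.3.* Blinding is limited to oxygen/sham in phase 2.
4. *Unblinding criteria (4.2).* The exceptions cover events that "require immediate knowledge on oxygen or sham treatment". The rule therefore concerns treatment and does not imply that altitude is masked in phase 1.
5. *Section 8.3.* "Before analysis, data are anonymized by allocating a numerical code to each participant". The code belongs to the participant, so recordings from 490 m and 2702 m carry the same code, and nothing says their location or date is removed.

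None of the five hides altitude.

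**Which outcomes depend on a reader.** Pulmonary pressure from the jet velocity, chamber dimensions, sleep staging and arousals, and apnea/hypopnea count and type do. Mean and minimal SpO2 and transcutaneous PCO2 come from instruments. The 6-minute walk distance is not taken from a stored recording.

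**Sensitivity of the pressure estimate (illustration only).** The formula is the protocol's, P = 4v². The 0.1 m/s over-read and the velocities are assumptions. The change is 4[(v + 0.1)² − v²]:

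- v = 2.5 m/s: 4(6.76 − 6.25) = 2.04 mmHg
- v = 3.0 m/s: 4(9.61 − 9.00) = 2.44 mmHg
- v = 3.5 m/s: 4(12.96 − 12.25) = 2.84 mmHg

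This moves the mean altitude difference only if the over-read is systematic and confined to altitude recordings. Unsystematic reading error leaves the mean difference unbiased. No comparable calculation is possible for sleep events.

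**The case against.** The strongest reply is that the protocol already plans a masked reader of stored echocardiograms, and that clinical data can reasonably be taken to include the circumstances of the visit. On that view only a clarification is needed. The reading is possible, but the text does not establish it, and a masking rule should name the factor under test.

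On sleep, the objection is that the point rests on silence. The section does not say that scoring is manual or done later from stored files, and the numerical threshold, standard criteria and several signals for event type narrow the scorer's discretion. They narrow it without removing it: typing events still means judging patterns. It also stands that masking can only be partial, because section 3.1 describes periodic breathing at altitude, so the signals to be scored may themselves reveal where they were recorded.

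Stronger readings are tempting, but the documents do not support them:

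- *Readers did know the altitude, or the results are biased.* The protocol leaves this open; it does not say so. It does not use the term open-label for phase 1 either; that is an inference.
- *The protocol announced the direction for both outcomes.* It did so for sleep-related breathing disturbance (3.3). A rise in pulmonary artery pressure appears in the background (3.1) and an open question (3.2), not among the phase 1 hypotheses.
- *The bias could be a large share of the effect.* With an assumed true rise of 5 to 10 mmHg, the illustration would give 2.04/10 = 20% to 2.84/5 = 57%. The documents give neither the rise nor the reading error, and the upper end pairs the highest velocity with the smallest rise.
- *The damage would be permanent.* Statistical analysis could not remove it, but the echo data are stored, so a masked re-reading remains possible.

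**Conclusion.** The point holds in a limited form. No provision hides altitude from the readers in phase 1, and the one masking rule for stored recordings omits it. This allows avoidable detection bias in estimated pulmonary artery pressure, cardiac dimensions, and apnea/hypopnea count and type. All are secondary outcomes; the primary outcome and the instrument-derived SpO2 and PCO2 are untouched.

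The size of any bias cannot be derived from the documents. The 2.0 to 2.8 mmHg range shows only how strongly the squared formula responds to an assumed systematic 0.1 m/s shift. It does not predict what happened or will happen.

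The conclusion assumes that clinical data carries its ordinary meaning and that sleep scoring involves human judgement. Who reads recordings, and what that person may know, is trial conduct that the protocol itself addresses, so the point is not one to leave to an analysis plan. It is worth acting on mainly because the remedy is cheap.

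**What to change.** Replace the echo sentence in section 6.1 with wording such as: *Stored echocardiograms are coded per recording, with location, date and visit removed, and read in random order by an investigator blinded to altitude, sequence and treatment; one reader reads all recordings of a given patient.* The reader already planned can do this.

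Add the same coding and random order to the sleep section, for the existing scorers. While apneas and hypopneas are marked, hide SpO2, end-tidal and transcutaneous PCO2, and cerebral near-infrared spectroscopy. The stated event rule needs none of them. Say openly that masking of sleep scoring is partial, because the breathing pattern may reveal altitude.

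Timing: the synopsis reports that COPD phase 1 was performed in 2013, so the amendment acts on phase 1 in PH and ILD patients (Table 1, from 2014) and on phase 2 reading. The 2013 COPD echocardiograms can be re-read masked from the stored data.

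The cost is relabelling, hiding channels during event marking, and a delay in reading until a patient's recordings are pooled. No patient procedure, visit or sample size changes.

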#### **Secondary outcomes**

- Exercise performance
  - o 6 min walk test: (distance is primary outcome) oxygen saturation and pulse rate at beginning/end
  - o Spiroergometry (1650 m): Maximal work rate, V'O2max; physiologic correlates of exercise limitation, i.e., heart rate, breathing reserve, inspiratory capacity, arterial blood gases
  - o Muscle oxygenation during submaximal exercise (2590 m)
- Subjective well-being
  - o Perceived exertion (Borg CR 10 scale at the end of a 6 min walk; modified MRC dyspnea score)
  - o acute mountain sickness (environmental symptoms cerebral score, AMS-c)
- Pulmonary function
  - o Lung volumes, diffusing capacity, arterial blood gases, maximal respiratory pressures
- Cognitive and psychomotor performance
  - o Psychomotor vigilance reaction time and number of lapses
  - o Trail making time
  - o Vestibular-ocular reflex gain and catch-up saccade pattern
- Cardiovascular and cerebrovascular function
  - o Arterial blood pressure; baroreflex sensitivity; heart rate/heart rate variability
  - o Indices of cerebrovascular auto-regulation and oxygenation measured by Doppler ultrasound and Near-infrared spectroscopy (2590 m only)
  - o Echocardiography: estimated pulmonary artery pressure, left and right atrial and ventricular dimensions and motion
- Sleep study and subjective sleep quality

- Mean and minimal oxygen saturation, oxygen desaturations >3%, transcutaneous PCO2, prevalence and type of central and obstructive apnea/hypopnea, heart rate
- Subjective sleep quality assessed by a visual analog scale

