## **5 PARTICIPANT ENTRY**

### **5.1 RECRUITMENT**

Patients diagnosed with stable COPD, PH or ILD will be asked to participate. They will be recruited among patients attending the Pulmonary Division University Hospital of Zurich and by advertisements distributed to the Zurich Lung League “Lunge Zürich” and newspapers.

During pre-study screening (recruitment examination), a detailed medical history and review of medical records will be performed to identify any risk factors that may predispose to adverse altitude effects (see exclusion criteria). Pulmonary function, arterial blood gases, resting ECG and a 24 h ambulatory pulse oximetry at the patient’s home will be obtained.

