### **5.3 EXCLUSION CRITERIA**

- Unstable condition and COPD exacerbation defined as a change in the dyspnea, cough or sputum production beyond normal day-to-day variation, acute in onset and which may require a change in treatment; a change in baseline medication within the last 30 days.
- Very severe COPD (i.e. GOLD 4, FEV1<30% predicted), severe gas exchange or hemodynamic impairment: diffusing capacity <30% predicted; hypoxemia requiring oxygen therapy at sea level ( $\text{PaO}_2 < 7.3 \text{ kPa}$ ); hypoventilation ( $\text{PaCO}_2 > 6.7 \text{ kPa}$ ); mean pulmonary artery pressure measured by right heart catheter >40 mmHg or pulmonary artery systolic pressure estimated by echocardiography >50 mmHg.
- Patients with very severe PH, NYHA class 4, unstable PH defined by a change of specific drug therapy within the last 30 days, hypoxemia requiring oxygen therapy at sea level ( $\text{PaO}_2 < 7.3 \text{ kPa}$ ); at 490m.
- Patients with very advanced ILD, NYHA class 4, unstable or exacerbated ILD, hypoxemia requiring oxygen therapy at sea level ( $\text{PaO}_2 < 7.3 \text{ kPa}$ ).

- More than mild or inadequately controlled cardiovascular disease such as uncontrolled systemic arterial hypertension, coronary artery disease, previous stroke; obstructive sleep apnea syndrome (overlap syndrome); pneumothorax in the last 2 months.
- Use of drugs that affect respiratory center drive (sedatives or sleep inducing drugs, morphine or codeine derivatives).
- Internal, neurologic or psychiatric disease that interfere with protocol compliance including current heavy smoking (>20 cigarettes per day), inability to perform bicycle exercise.
- Previous intolerance to moderate altitude (<2600m).
- Exposure to altitudes >1500m for >2 days within the last 4 weeks before the study. Pregnant patients (women potentially capable of childbearing, i.e., who are not yet menopausal and had their last menstrual period less than 12 months ago, who had no hysterectomy, ovariectomy, or surgery to occlude the fallopian tubes, will be tested for pregnancy, on site, at the beginning of the study, by urinary  $\beta$ -HCG-concentration (lifeSign Status hCG Serum/Urine). The urine sample will not be stored.)
- Nursing patients.

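### The echocardiographic 'systolic pulmonary artery pressure' is computed without right atrial pressure, so the secondary outcome is a tricuspid gradient under the wrong name, and the quantity behind the 50 mmHg exclusion limit is left open

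*Protocol*

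**What the plan says.** In Protocol section 6.1, under the specialized cardiovascular evaluation, the echocardiography paragraph lists "systolic pulmonary artery pressure (RVsys, calculated from the tricuspid regurgitation velocity by using the modified Bernoulli equation". The formula printed there is RVsys = 4 × (vmax)², where vmax "is the maximum of the regurgitation velocity jet measured over the tricuspid valve". It has no other term, and right atrial pressure is not mentioned anywhere else in the protocol.

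The quantity appears, or may appear, in two further places:

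- **Outcome.** Sections 4.1 and 8.1 list "Echocardiography: estimated pulmonary artery pressure" among the secondary cardiovascular outcomes.
- **Eligibility.** Section 5.3 excludes patients with "mean pulmonary artery pressure measured by right heart catheter >40 mmHg" or "pulmonary artery systolic pressure estimated by echocardiography >50 mmHg". Both limits stand in the bullet that opens with very severe COPD. The separate PH and ILD bullets do not repeat them. Section 5.3 neither gives a formula nor refers to section 6.1.

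On the source of the eligibility value, section 5.1 lists the recruitment measurements: "Pulmonary function, arterial blood gases, resting ECG and a 24 h ambulatory pulse oximetry at the patient’s home will be obtained". Echocardiography is not among them. The same paragraph also says that "a detailed medical history and review of medical records will be performed to identify any risk factors".

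**The concern.** The Bernoulli relation turns the velocity of a jet into the pressure drop across the opening it passes through. For the tricuspid regurgitation jet, that drop is right ventricular minus right atrial systolic pressure. To obtain right ventricular systolic pressure, and from it pulmonary artery systolic pressure, right atrial pressure must be added back. The protocol gives the gradient the name of the full pressure.

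Two things are at stake. The first is the absolute level of a reported outcome. The protocol treats a rise in pulmonary artery pressure as a candidate mechanism of altitude intolerance in all three patient groups (section 3.1), so readers will compare the reported levels with pressures from other sources. The understatement is not a fixed constant. It equals each patient's own right atrial pressure and so is largest where that pressure is raised. Section 3.1 notes that right heart failure may develop as PH progresses.

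The second is the meaning of the 50 mmHg limit. The protocol contains one echocardiographic formula and one echocardiographic limit and does not say whether they belong together. If they do, the limit acts on the gradient and admits some patients whose named pressure exceeds 50 mmHg.

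**Working it through.** The plan states no figure that could be reproduced, so the check works from the printed formula and the printed limit.

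**Inputs**
- Formula: P = 4 × v², with v the peak tricuspid jet velocity in m/s and P in mmHg (section 6.1).
- Limit: 50 mmHg (section 5.3).
- Right atrial pressure (RAP): not given in the protocol. Values of 5, 10 and 15 mmHg are assumptions used to show a range.

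**Step 1. Velocity at which 50 mmHg is reached**

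Printed formula: v = √(50/4) = √12.5 = 3.54 m/s.

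With RAP added, P = 4 × v² + RAP, so v = √((50 − RAP)/4):

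| Assumed RAP (mmHg) | Calculation | v (m/s) | 4 × v² + RAP when 4 × v² = 50 (mmHg) |
|---|---|---|---|
| 5 | √(45/4) | 3.35 | 55 |
| 10 | √(40/4) | 3.16 | 60 |
| 15 | √(35/4) | 2.96 | 65 |

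**Step 2. One patient in the gap**

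At v = 3.4 m/s the printed formula gives 4 × 11.56 = 46.2 mmHg, below the limit. With RAP added, the value is 51.2, 56.2 or 61.2 mmHg, above the limit in all three cases.

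**Step 3. Effect on the outcome**

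- Absolute value: (4 × v² + RAP) − 4 × v² = RAP. The reported level is too low by exactly RAP.
- Within-patient change between conditions 0 and 1: [4 × v₁² + RAP₁] − [4 × v₀² + RAP₀] = 4 × (v₁² − v₀²) + (RAP₁ − RAP₀). The printed formula keeps only the first term, so its error is RAP₁ − RAP₀. This is zero if right atrial pressure is the same in both conditions.

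**Step 4. Where the limit could be checked before ascent**

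- Section 5.1 names no echocardiogram but does require a review of medical records.
- Table 3 places echocardiography at 14:30 on day 2 of a stay and describes assessments as similar across locations.
- In phase 2 (Tables 4 and 4a) both sequences begin at 490 m, so the Zurich echocardiogram precedes the first ascent. Randomization, however, belongs to the screening block before it.
- The sequences that begin at altitude are C and D of Table 2 (COPD phase 1, already performed in 2013 according to the synopsis) and sequence B of Tables 2a and 2b (PH and ILD).
- Figures 2, 2a and 4 have an echocardiography row and a recruitment-day column, but the marking of the cells is not readable in the text at hand.

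**The case against.** The strongest defence is that this is a matter of terminology. The formula is printed in full, the abbreviation RVsys points to the ventricle, and sections 4.1 and 8.1 call the pressure estimated. Section 8.3 analyses altitude and oxygen effects as cross-over contrasts, in which a constant right atrial pressure cancels (step 3). That last argument stands for changes, and nothing in the protocol shows that right atrial pressure changes with altitude or oxygen. It does not rescue the absolute values. RVsys is also no better a label, because the expression is not right ventricular pressure either.

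Several stronger readings are tempting, but the document does not support them:

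- **A reader might infer that the exclusion actually runs on the gradient and that every patient between the two velocities is misclassified.** Section 5.3 does not cite the formula, and section 6.1 describes study measurements. A value taken from a clinical report would follow that report's own method, and the catheter criterion in the same bullet could still exclude the patient. The velocities in step 1 therefore hold only on the condition that the section 6.1 formula is used.
- **A reader might infer that patients ascend before the limit can be checked.** Record review may supply a value, and a recruitment-day echocardiogram cannot be ruled out because the cells of Figures 2, 2a and 4 cannot be read. COPD phase 1 is complete, and phase 2 starts at 490 m. The altitude-first sequences still planned concern PH and ILD patients, whose own bullets set no pulmonary pressure limit. What stands is that section 5.1 names no source for a value that section 5.3 requires.
- **A reader might take 5 to 15 mmHg as the established shortfall.** It is an assumed range.

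**Conclusion.** The definition in section 6.1 is wrong as written. Computed that way, the secondary outcome is the tricuspid pressure gradient, and its absolute values fall short of the named pressure by each patient's right atrial pressure. For an assumed 5, 10 or 15 mmHg, the shortfall is that same 5, 10 or 15 mmHg. The altitude and oxygen contrasts are affected only by any change in right atrial pressure between conditions.

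The eligibility part is conditional. If the echocardiographic limit is evaluated with the protocol's only formula, it is reached at 3.54 m/s instead of 3.35, 3.16 or 2.96 m/s under the same assumptions. Whether it is evaluated that way, and whether it extends beyond COPD, the protocol does not say. That silence is itself what sections 5.1, 5.3 and 6.1 need to resolve.

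The 6 minute walk distance and the sample size in section 8.2 are not touched. The point deserves correction because it is simple and concerns a reported outcome, but it does not threaten the main conclusions of the trial.

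**What to change.** 1. **Make name and formula agree.** Either call the quantity the tricuspid regurgitation pressure gradient in sections 4.1, 6.1 and 8.1, or define systolic pulmonary artery pressure as 4 × (vmax)² plus a right atrial pressure estimate from the same echocardiogram, and state how that estimate is made. Apply one definition to all phases and patient groups.
2. **Reconcile sections 5.1, 5.3 and 6.1.** State which quantity the echocardiographic limit refers to, which patient groups it covers, and from which source (existing report or study examination) it is checked before entry. The value of the limit is for the sponsor to state.

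Renaming costs only wording. It also covers data already collected, since section 6.1 says the echocardiography data are stored. Adding a right atrial pressure estimate brings in the imprecision of that estimate. For recordings already made, it also depends on whether the images it needs were taken, which the protocol does not say. Where they were not, the gradient label is the safer choice.
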